#### Aim III

To determine if daily-life mobility changes after interventions, our main analysis will be the paired t-tests to compare the values in each metric described in Table 4 in the pre and post-exercises, separately. We will use the same statistical procedures as described in Aim II to explore improvement (estimated) between groups since no study has investigated the effects of any intervention on daily-life mobility using instrumented socks with wearable sensors.

Missing data: We will first assess the missing data frequency and patterns for both primary outcomes. If ≤ 5% of observations are missing the primary outcome, then multiple imputation methods will not be of benefit and we will perform analysis without imputation. If > 5% of observations are missing outcomes, we will perform multiple imputations as necessary to address the missing-ness. For all analyses, level of significance will be set at *p* ≤ 0.05.

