How an exercise program is delivered is important. We previously compared the Agility Boot Camp (ABC) exercise intervention executed via one-on-one, delivery with the physical therapist in the clinic versus at-home, unsupervised exercises (standard of care) [28]. The ABC framework targeted the underlying constraints on balance in people with PD including rigidity, bradykinesia, freezing, inflexible program selection (segmental coordination), impaired sensory integration, and reduced executive function and attention. Not surprisingly, the one-on-one, in-clinic delivery of the ABC program improved balance better than unsupervised at-home ABC [28]. We found that the Mini-BESTest had a large improvement (effect size = 0.86) after 12 sessions of in-person ABC rehabilitation and only a moderate improvement (effect size = 0.67) in the unsupervised, home exercise group [28]. In fact, the unsupervised home group improved very little across all outcome measures, while the in-person group improved the most on function and balance measures [28]. In the current study, we will adapt our original ABC program, designed to target underlying constraints on balance, to be performed virtually with appropriate safety modifications. We hypothesize that a virtual delivery of the ABC exercise program, called Tele-ABC, will be more effective than the unsupervised-ABC program in improving balance. In addition, we will explore the role of cognition, both as a potentially important covariate for successful participation in telerehabilitation and as an outcome measure after rehabilitation since executive and visuospatial functions are linked to balance [29–32], and are very important to daily-life mobility in PD. The Tele-ABC exercise program also uses embedded balance and cognitive exercises simultaneously which may improve cognition of people with PD.

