Another major focus in rehabilitation care is the advancement of using objective measures to quantify movement. Our group [33] and others [34, 35] have demonstrated that objective measures of balance and mobility are more sensitive to change compared to standard clinical measures after rehabilitation. Also, we know that the assessment of mobility in the clinic may not adequately reflect mobility during daily life, accurate measurements of walking and turning in daily life represent a technical challenge from both an algorithm standpoint and the storage of the large amount of data generated [36]. We recently demonstrated that quality, but not quantity, particularly turning and foot-strike angle, in daily life, is impaired in people with PD compared to similar age control participants [37, 38]. Here we will use wearable sensors worn during daily life to measure if Tele-ABC improves mobility in every day life. We hypothesize that gait quality measured during daily life will improve after balance telerehabilitation.

The present trial has three aims: I) *virtual assessment*: to determine if a virtual balance assessment (instrumented L-shape mobility test) with wearable sensors can predict a gold-standard clinical in-person assessment of balance, the Mini-BESTest; II) *virtual rehabilitation at home*: to explore the effects of 12 sessions of Tele-ABC (experimental group) and unsupervised-ABC (control group) on balance, gait, instrumented executive function tests, and clinical scales; and III) *home monitoring after telerehabiliation*: to explore if improvements after balance telerehabilitation transfer to daily-life mobility, measured by wearing instrumented socks for 7 days.

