#### Aim III

One of the goals of Aim III is to generate preliminary estimates of effect size for daily life metrics measured in the home after rehabilitation, for both the groups (experimental and control). These estimates ultimately will be used to inform power and sample size computations for a larger clinical trial. Specifically, we will calculate effect size estimates from 5 main home metrics that are predicted to be the most likely to show improvement after rehabilitation (turn angle, swing variability [coefficient of variation], the angle at heel strike, the angle at heel strike variability [coefficient of variation], and stride length variability [coefficient of variation]). Using paired sample t-tests, we estimate that we will have at least 80% power to detect pre/post differences with moderate effect sizes (Cohen’s d = 0.45) or greater with 40 participants at an alpha level of 0.05.

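### Aim III ranks the within-arm paired t-test above the randomised between-arm comparison and bases its power on one arm, so its main test cannot attribute a change in daily-life mobility to telerehabilitation

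*Protocol article*

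**What the plan says.** The Introduction of the protocol article gives the third aim as "to explore if improvements after balance telerehabilitation transfer to daily-life mobility". The matching hypothesis is that daily-life gait quality improves after telerehabilitation, and it names no comparator. The last paragraph of the Discussion goes further and describes the trial as designed to determine that translation.

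Under Statistical analysis, Aim III, the ranking is explicit: "our main analysis will be the paired t-tests to compare the values in each metric described in Table 4", before against after exercise, separately. The between-arm work follows in the next sentence: "We will use the same statistical procedures as described in Aim II to explore improvement (estimated) between groups". The Aim II procedures it refers to are a mixed model with a group-by-time term, an analysis of covariance on change controlling for baseline, and independent t-tests on change with an effect size and confidence interval.

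Under Sample size calculation, Aim III, power rests on the paired test: "Using paired sample t-tests, we estimate that we will have at least 80% power to detect pre/post differences with moderate effect sizes", with "d = 0.45) or greater with 40 participants at an alpha level of 0.05". The same section plans effect sizes for each of the two groups and says of them: "These estimates ultimately will be used to inform power and sample size computations for a larger clinical trial".

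The Intervention section states that both arms receive the same exercises. Delivery is what differs: real-time remote supervision in one arm, and an unsupervised home programme after one in-person session in the other.

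**The concern.** A before-after test in one arm answers whether that arm changed. It does not answer whether telerehabilitation caused the change. The difference between two 7-day recordings, taken either side of about 4 weeks of exercise, contains any programme effect together with whatever else differs between first and second wear. The control arm is there to remove that common part. Because that arm does the same exercises, only the between-arm contrast isolates what supervised remote delivery adds.

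With the paired test as the main analysis, a claim that gains after telerehabilitation carry over to daily life could rest on a result that randomisation does not protect. The power statement adds to this. A reader sees 80% at a moderate effect size and may take it to describe the randomised comparison, which it does not.

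**Working it through.** **Inputs.** From Sample size calculation, Aim III: d = 0.45, n = 40, alpha 0.05. From Recruitment, randomization, and allocation: 40 per arm, 1:1. Assumptions, since the article does not state them: two-sided tests, d expressed in SDs of the change score, equal SDs of change in both arms, and no dropout.

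**1. Reproducing the stated power.** For a paired t-test the non-centrality is d × √n = 0.45 × √40 = 2.846 on 39 degrees of freedom. The non-central t gives 79.3% power. The normal approximation gives Φ(2.846 − 1.960) = 81.2%. The effect that gives exactly 80% is d = 0.454. The stated figure is therefore reproduced to within 2 points. If all 80 participants were pooled, the non-centrality would be 0.45 × √80 = 4.025 and power 97.8%. The calculation is thus for one arm. This also settles the slightly ambiguous word at the end of the Aim III analysis sentence: the paired tests are within arm.

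**2. What the main test does when the arms do not differ.** Let both arms have the same true change d, so that the effect of randomised assignment is zero. The chance that the Tele-ABC paired test is significant is its power at d:

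| Shared change (SD of change) | Non-centrality, d × √40 | Tele-ABC paired test significant |
|---|---|---|
| 0.20 | 1.265 | 23.5% |
| 0.30 | 1.897 | 45.7% |
| 0.45 | 2.846 | 79.3% |

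A two-sample t-test on the change scores keeps its 5% level whatever the shared change. A simulation of 100,000 trials at 0.45 gave 4.9%. The shared shifts are assumptions. Only 0.45 is in the article, where it is a design effect and not an estimate of drift.

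**3. Power of the between-arm comparison.** For a difference δ in mean change, with 40 per arm, the non-centrality is δ × √(40/2) on 78 degrees of freedom.

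- At δ = 0.45: 0.45 × 4.472 = 2.012, giving 51.1% power.
- 80% power needs δ = 0.634.
- 80% power at δ = 0.45 needs about 79 per arm.
- If the Tele-ABC arm changes by 0.45 and the control arm by 0.15, 0.225 or 0.30 (assumed), δ is 0.30, 0.225 or 0.15, and power is 26%, 17% or 10%.

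**4. Effect of baseline adjustment.** With equal pre and post SDs and pre-post correlation ρ, adjusting for baseline multiplies the SD of change by √((1 + ρ)/2). The article gives no ρ for these metrics. At an assumed ρ of 0.5 the factor is √0.75 = 0.866, and the detectable difference falls to 0.634 × 0.866 = 0.55 SD of change. At an assumed ρ of 0.9 the factor is √0.95 = 0.975, giving 0.62. Adjustment helps, but does not restore 80% power at 0.45 in this range.

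**The case against.** Much of the case on the other side stands.

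- **The control is used.** A reader might infer that Aim III throws the control arm away. It does not. The Aim II between-arm procedures are applied, and the daily-life metrics in Table 4 are also secondary outcomes examined under Aim II. The fault lies in the ranking and the power basis.
- **No cross-arm reading of p-values is planned.** A reader might infer that significance in one arm and not in the other will be taken as a difference. Nothing in the article proposes this.
- **The next trial is not bound to receive the wrong effect size.** Aim II plans a between-group effect size with a confidence interval and sends the pilot's estimates to the future sample size. Means and SDs of change per arm would also yield the between-arm difference. What remains is that the Aim III sample size section describes effect sizes by group and does not say which estimate will be carried forward.
- **Equal change in both arms is not necessarily spurious.** Both arms train, so it could be real carry-over of exercise. The paired test cannot tell this from time effects, and cannot credit it to remote delivery.
- **The article does not show that controls will improve in daily life.** The earlier result, "only a moderate improvement (effect size = 0.67) in the unsupervised, home exercise group", concerns the Mini-BESTest, and the next sentence says that the home group gained little over the outcomes as a whole. It shows only that a static control arm should not be assumed.
- **Some sources of drift are weak here.** No eligibility criterion selects on a sensor metric, monitoring is passive, and about 4 weeks leaves little room for season.

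The hypothesis also names no comparator, so a paired test does fit its literal wording. It does not fit the Discussion's claim about translation after telerehabilitation.

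**Conclusion.** The point holds in limited form. The main Aim III test and its power calculation concern change within one arm, and the comparison that randomisation supports is ranked as exploratory. The main test would be significant in about 79% of trials if both arms changed equally by the design effect of 0.45 SD, and in 46% or 24% at 0.3 or 0.2 SD, against about 5% for the between-arm test. These figures assume two-sided testing, equal SDs of change, no dropout and the stated shared shifts, whose true size is unknown. The stated 80% power is correct for what it describes. For a between-arm difference of the same size, unadjusted power is about 51%.

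The weight is moderate. The trial is a pilot, the aim is worded as exploratory, the outcomes are secondary, and the primary outcome is compared between groups.

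**What to change.** 1. In Statistical analysis, Aim III, name the between-arm estimate as the main analysis: the analysis of covariance on change controlling for baseline that Aim II already specifies, reported as an adjusted difference with 95% confidence interval. State that any claim about telerehabilitation and daily-life mobility rests on it.
2. Keep the paired pre-post changes, by arm, as descriptive results.
3. In Sample size calculation, Aim III, say that 80% power at d = 0.45 applies to within-arm change only. Add that 40 per arm gives about 51% unadjusted power for a between-arm difference of 0.45 SD of change and 80% at about 0.63 SD, and that baseline adjustment improves on this.
4. In the same section, say that the adjusted between-arm difference, with the SD of change and the pre-post correlation, is what will size the larger trial.

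The change needs no new data, visits or models. Its cost is a less favourable power figure, and the likelihood that Aim III yields a wide interval instead of a significant result. For a pilot meant to inform a larger trial, that interval is the more useful product.

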## Discussion

Telerehabilitation is now commonly used for patients with PD, but there are several unknown aspects of its efficacy, both for the assessment and treatment of balance deficits in people with PD. In addition, studies on balance telerehabilitation (separate from virtual reality) for people with PD are scarce. For telerehabilitation to be effective, both assessment and treatment should be able to be completed virtually. The TelePD Trial targets both virtual assessment and treatment for balance problems in people with PD.

Regarding assessment, no virtual comprehensive balance assessment has been conducted pre and post-telerehabilitation in people with PD [18]. A gold standard clinical test is the BESTest [60], which evaluates balance across domains. The Mini-BESTest, a shorter version, is the most widely used balance assessment tool in physical therapy clinics and research protocols [43, 61]. While the Mini-BESTest, a clinical measure, has been studied extensively and for PD has been shown to be reliable and valid both for measuring multiple domains of balance [61], measuring balance domains in a virtual setting is unexplored. We recently published data showing that instrumented balance and gait tests using wearable sensor technology can successfully quantify different domains of balance and gait in older adults [11]. Both clinical (Mini-BESTest) and ISAW measure independent domains of balance and gait (Table 4). Thus, we will use wearable sensors to determine if we can predict Mini-BESTest scores (as the clinical, in-person, gold standard) using the instrumented L-shape mobility test to objectively and remotely quantify balance across domains in people with PD. As balance is particularly challenging to assess virtually, clinical maneuvers or sophisticated equipment are not available in people’s homes, our study will help determine if a simple but objective balance and gait assessment can be applied virtually in future telerehabilitation trials or for a virtual balance evaluation. Furthermore, patients with cognitive impairment may be less responsive to a virtual approach- both assessment and/or intervention.

Regarding treatment, effective balance rehabilitation requires precise targeting of the impaired domain in order to ultimately treat the underlying deficit in balance dysfunction [43, 60, 62, 63]. Although we have previously demonstrated improvements after ABC in-person rehabilitation [33], the potential for administering this PD-specific, constraint-focused program virtually is unknown. Further, it is unknown if improvements after rehabilitation carry over to improvements in daily-life mobility. Passive monitoring of mobility during daily life can provide important measures of turning and variability that are difficult to detect in regular clinical scales [36–38] and may be sensitive to change after rehabilitation. An important aspect of continuous, passive monitoring, is the ability to measure variability in performance over time, which has previously been shown to be sensitive to early versus moderate PD [37, 64–66], fall frequency [67], and mild cognitive impairment in PD [68]. Specifically, we found that turning variability over the day and week was higher in people with PD compared to healthy controls, and variability measures increased with disease severity. Although studies have quantified gait and turning in daily life with wearable technology [64, 69, 70], including an association with falls and cognition, the effects of telerehabilitation on daily-life mobility are unknown.

The TelePD trial is designed to determine the usefulness of using wearable sensor-based measures of balance and gait remotely to assess balance, the feasibility and efficacy of balance telerehabilitation in people with PD, and the translation of balance improvements after telerehabilitation to daily-life mobility. The successful implementation of the TelePD Trial will shed further light on balance telerehabilitation interventions for people with PD. The long-term goal of this project is to develop an effective, virtual balance assessment and evidence-based treatment that can be used in any older adult with balance impairments.

## Data Availability

Data sharing is not applicable to this article as no datasets were generated or analyzed during the current study. The final results of this study will be published in peer-reviewed journals.

## Abbreviations

PD: Parkinson’s disease
TelePD: Telerehabilitation Parkinson’s Disease Trial
OHSU: Oregon Health & Science University
SPIRIT: Standard Protocol Items: Recommendations for Interventional Trials
Mini-BESTest: Mini Balance Evaluation Systems Test
ISAW: Instrumented Stand and Walk Test
MDS*-*UPDRS: Movement Disorder Society-Sponsored Revision of the Unified Parkinson's Disease Rating Scale
ABC: Activities-Specific Balance Confidence
PDQ-39: Parkinson's Disease Questionaire-39
REDCap: Research Electronic Data Capture system
NfoGQ: New Freezing of Gait Questionnaire
FES-I: Falls Efficacy Scale-International
IPAQ: International Physical Activity Questionnaire- Short Form
TSS: Telerehabilitation Satisfaction Scale
HEP: Home Exercise Program
PGIC: Patient Global Impression of Change
TabCAT: Tablet-based Cognitive Assessment Tool
